### Process evaluation

Participants complete a short survey online each week to measure mediating variables relevant to the process of change. The battery includes the TSK, PDI, IPAQ, QBPDS, a numeric rating scale assessing pain severity, and an 11-item scale assessing coping with pain, self-efficacy and avoidance rated on an 11-point scale.

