#### Research questions

1) Is EXP more effective (at post-treatment and at six-month follow-up) at reducing pain-related disability and pain intensity (primary outcomes) as well as other symptoms compared to CBT-P in patients with fear-avoidance beliefs?

2) Are there any differences in treatment effects between the short (10 sessions) and the long (15 sessions) versions of exposure at post-treatment and at six-month follow-up?

3) What is the cost-effectiveness of EXP as compared to CBT-P?

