#### Primary outcome measures

Pain-related disability is measured using the Pain Disability Index (PDI) [29,33] and the Quebec Back Pain Disability Scale (QBPDS) [25].

Pain intensity is assessed four times a day using a two-week pain diary comprising an 11-point numeric rating scale (NRS) (0 = no pain, 10 = pain at its worst) and an 11-point scale from the German Pain Questionnaire (Deutscher Schmerzfragebogen,DSF) assess average pain intensity during the past four weeks [34].

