### Data collection

Data are collected at baseline (T0), after 10 sessions (T1, completion of EXP short), upon completion of the intervention (T2), and six months following completion of treatment (T3). Thus, participants in the short version of EXP complete only three assessments. Questionnaires are completed at home via the internet. This procedure reduces missing data and helps to keep study therapists blind to outcome data. Supplemental evaluations are carried out weekly, including process variables. If patients do not have internet access the assessment are provided on a computer in our outpatient clinic. Video recordings are carried out during each session to gather objective data for later analysis of treatment fidelity.

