### Data analysis

The latest version of The Statistical Package for Social Science (IBM SPSS Statistics) version 19is used for data analyses. Intention-to-treat analyses (ITT) used to account for deviations from random allocation and missing data. A repeated measures design will be used with primary and secondary measures as dependent variables, group as the between-subjects factor, and time of measurement as the within-subjects factor.

Possible confounding variables (for example, duration of complaints) will be considered and included as covariates according to the results of correlation analyses. Effect sizes (Cohen´s d) will be calculated to determine the magnitude of the mean differences between groups on the outcome variables. According to Cohen´s guidelines, an effect size of .2 indicates a small effect, .5 a medium effect and .8 a large effect [52]. We consider a 30% reduction on the NRS to indicate clinically important change on the core outcome measure of pain intensity [53]. The economic evaluation consisted of a cost-utility analysis and a cost-effectiveness analysis. For both analyses, the incremental cost-effectiveness ratio (ICER) was calculated as (C1-C0)/(E1-E0) where C is the cost and E is the effect and the experimental and comparator conditions are indexed with the 1, 0 subscripts.

The incremental cost-utility ratio will focus on the net costs per quality adjusted life years (QALY) gained. The cost-effectiveness ratio focuses on the net costs per reliable and clinically improved case of disability/pain. Probit analysis will be used for dose–response effects. This approach based on probability theory and includes determining the observed rates and resulting probability of a response for a particular treatment.

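### Weekly PDI and QBPDS scores have no stated role in handling dropout, although they could replace carry-forward for the primary disability outcome

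*Protocol article*

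**What the plan says.** Under Primary outcome measures, pain-related disability is assessed with the PDI and the QBPDS. Under Process evaluation, both scales appear again in a weekly online survey: "Participants complete a short survey online each week to measure mediating variables relevant to the process of change", and "The battery includes the TSK, PDI, IPAQ, QBPDS, a numeric rating scale assessing pain severity". No arm is exempted.

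Data collection sets the main assessments at T0, T1 (after 10 sessions), T2 (completion) and T3 (six months later). Because T1 is already the end of treatment for short exposure, "participants in the short version of EXP complete only three assessments". The weekly data are placed outside this schedule: "Supplemental evaluations are carried out weekly, including process variables".

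On analysis, "A repeated measures design will be used with primary and secondary measures as dependent variables", with "group as the between-subjects factor, and time of measurement as the within-subjects factor". The occasions that make up the time factor are not listed. Sample size calculation states an intention-to-treat analysis with the last value carried forward. It does not say whether a weekly score can be that last value. Research questions asks for effects at post-treatment and at six months.

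**The concern.** The best information on a patient who leaves during treatment is that patient's own recent score on the outcome scale. This trial collects it every week, yet the stated rule for missing outcomes makes no mention of it. On the schedule in Data collection, short exposure has no value between baseline and the end of treatment, so anyone lost in between is analysed as unchanged from baseline.

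Two things are at stake. Carrying baseline forward distorts the arm means for disability, by an amount that depends on how many patients leave each arm and when. Replacing it with a mixed model on the scheduled visits alone would not fully cure this. If leaving depends on how the patient was doing that week, the data are missing at random given the weekly scores but not given T0 alone.

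**Working it through.** **1. What is known about a patient who is lost.** Appointments are weekly, so week and session number are treated as the same. The last column assumes that carry-forward works on the scheduled visits.

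| Arm and time of loss | Scheduled values | Weekly PDI/QBPDS | Value carried forward |
|---|---|---|---|
| Short exposure, after week 8 | T0 | up to 8 | baseline |
| 15-session arm, after week 8 | T0 | up to 8 | baseline |
| 15-session arm, after week 12 | T0, T1 | up to 12 | T1 |

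Early losses are treated alike in all arms. The third row has no counterpart in short exposure, where every on-treatment loss falls back to T0.

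**2. Carrying baseline forward.** If a fraction p of an arm is lost before its next scheduled visit, and loss is unrelated to the score, the error in that arm's end-of-treatment mean is p × g, where g is the true mean improvement. Both are assumptions, as the article gives neither. With g = 0.8 SD:
- p = 0.15: 0.15 × 0.8 = 0.12 SD
- p = 0.25: 0.25 × 0.8 = 0.20 SD

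In both cases the arm looks worse than it is. If loss depends on the weekly score, simulation gives 0.06-0.29 SD: the low end when patients doing worse than expected leave, the high end when patients doing better leave.

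**3. A likelihood model on scheduled visits only.** Simulation of one short-exposure arm over weeks 0-10, with 200,000 patients so that sampling error is negligible. Assumptions:
- Total variance 1, made up of a random intercept (0.45-0.50), an autoregressive part (0.25-0.40, weekly correlation 0.87-0.90) and error for the rest.
- Adjacent-week correlation therefore from 0.45 + 0.25 × 0.88 = 0.67 to 0.45 + 0.40 × 0.87 = 0.80.
- Loss in weeks 4-9, with log-odds changing by about 1 per SD of that week's deviation from what T0 predicts, in either direction.

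| Lost | Error, scheduled visits only | Error, weekly scores included |
|---|---|---|
| 15% | about 0.05-0.07 SD | under 0.01 SD |
| 25% | about 0.10-0.11 SD | under 0.01 SD |

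The sign follows who leaves. If patients doing worse leave, the visits-only model makes the arm look too good, whereas carrying baseline forward makes it look too bad. A stronger link between score and loss gives a larger error.

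**4. Scale.** With 36 per arm and the article's correlation of 0.5, the standard error of a baseline-adjusted difference at T2 with complete data is √(2 × (1 − 0.5²)/36) = √0.0417 = 0.204 SD. An error of 0.05-0.11 SD is 0.05/0.204 = 0.25 to 0.11/0.204 = 0.54 of that standard error. It is also 25-55% of the 0.2 that Data analysis calls a small effect.

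**5. Precision.** Variance of the two-arm difference, with unrestricted means by arm and occasion, a common baseline mean and known covariance; ratio of weekly scores added to scheduled visits only:
- T2, no dropout: 0.04167/0.04167 = 1.000.
- T2, dropout 10%: 0.975-0.985; 20%: 0.950-0.969; 30%: 0.925-0.952.
- T3, no dropout: 1.000; with 10-30% lost on treatment and 5-10% later: 0.91-0.99.

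With complete data the weekly scores add nothing to the planned contrasts. With dropout they lower the variance by roughly 1-9%. The case for using them is therefore bias from dropout, not precision.

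**The case against.** **The exclusion is an inference.** No sentence bars weekly scores from the effect analysis or from being the value carried forward, and a condensed article may leave this to a fuller plan. This stands in part. But the article does state the missing-data rule, counts only T0-T3 as assessments and calls the weekly data supplemental, so the scheduled-visit reading is the natural one. If a weekly score could be carried forward, the return to baseline would go, but carry-forward would remain.

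**The bias is assumed.** There is no dropout rate in the documents, and near-zero error with weekly scores follows from letting loss depend on those scores. Patients who stop treatment may still answer T1 and T2 online at home, and may stop the weekly survey before they leave. Similar early loss in all arms would partly cancel in the contrasts. All of this stands: the figures show what is at risk, not what will happen.

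**Stronger readings a reader might infer.**
- That the plan mislabels its primary outcome as a mediator. The Process evaluation wording invites this, but the Discussion names self-efficacy, pain coping and pain beliefs as the key mediators, and a mediation analysis needs the outcome measured alongside them.
- That the plan gives away substantial precision. With unrestricted means and complete data the gain is zero. Larger gains need an assumed smooth time course, which nothing in the article supports and which changing session content, especially in CBT, makes doubtful.
- That information between visits is discarded. T1 lies mid-treatment in both 15-session arms, and the weekly data feed the process evaluation.

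**Conclusion.** The point holds as one about dropout. The primary disability scales are measured weekly, but the plan gives those scores no stated role when an outcome is missing and relies on carry-forward. On the scheduled-visit reading, every short-exposure patient lost on treatment returns to baseline, while later losses in the 15-session arms keep T1, so the distortion can differ by arm.

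Under an assumed 15-25% score-driven loss, a visits-only likelihood model is off by about 0.05-0.11 SD in the affected arm, against under 0.01 SD with weekly scores. Carrying baseline forward is usually further off. These sizes rest on the assumed dropout, correlations and improvement, on weekly surveys being completed until the patient leaves, and on loss being explained by the observed weekly scores. With little dropout the point is minor. Nothing here challenges the sample size of 108 or shows a precision loss with complete data.

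**What to change.** In Sample size calculation and Data analysis, replace last value carried forward for PDI and QBPDS with one of two approaches, named in advance:
- a likelihood-based longitudinal model for each scale that includes T0, the weekly scores and T1-T3; or
- multiple imputation by arm, with the weekly PDI and QBPDS scores in the imputation model.

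Either way, keep unrestricted arm-by-occasion means at T1-T3 and read the same contrasts at completion and at six months. The weekly pain rating can be an auxiliary variable, but not a substitute for the primary pain outcome, because it is neither the two-week diary nor the German Pain Questionnaire item. State also that weekly scores remain available for the process evaluation.

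The cost is a few lines of text and somewhat more analysis work, with no new patients, visits or questionnaires. With up to 15 weekly scores and 36 patients per arm, a structured covariance or a reduced set of weekly predictors will be needed. Trial status reports 71 randomised by May 2013 with recruitment still open, so at that stage the rule could be fixed before analysis.

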### Economic evaluation

Costs and expenses are evaluated using an adapted version of the short form of the Trimbos/iMTA questionnaire for costs associated with psychiatric illness over the past month (TIC-P) [51]. The total costs include direct health-care and non-health care costs (that is, travel costs, out-of pocket expenses, self-paid medical care), as well as indirect health care costs due to loss of productivity. Direct health-care costs include costs of health-care consumption in general (that is, general practitioner, physical therapists, hospital visits and so on.). The number of consultations is multiplied by the cost of each visit to calculate total costs.

### Data collection

Data are collected at baseline (T0), after 10 sessions (T1, completion of EXP short), upon completion of the intervention (T2), and six months following completion of treatment (T3). Thus, participants in the short version of EXP complete only three assessments. Questionnaires are completed at home via the internet. This procedure reduces missing data and helps to keep study therapists blind to outcome data. Supplemental evaluations are carried out weekly, including process variables. If patients do not have internet access the assessment are provided on a computer in our outpatient clinic. Video recordings are carried out during each session to gather objective data for later analysis of treatment fidelity.

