**Methods:**

A total of 108 chronic low back pain patients are randomly assigned to one out of three conditions (A: exposure_long (15 sessions), B: exposure_short (10 sessions) or C: control condition cognitive behavioral therapy (15 sessions)). The inclusion criteria are: back pain ≥3 months and a sufficient level of fear-avoidance. An effect evaluation, a process evaluation and an economic evaluation are conducted. Primary outcomes are pain-related disability and pain intensity. Secondary outcomes are: emotional distress, fear avoidance, catastrophizing and costs. Data are collected at baseline, upon completion of the intervention, after 10 sessions, and at six months following completion of treatment. Besides the comparison of exposure *in vivo* and cognitive behavioral therapy (CBT), we additionally compare a short and a long version of exposure to analyze dose response effects.

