### Sample size calculation

To identify the target number of participants we used the G-Power Analysis software program (University of Düsseldorf, Germany http://www.psycho.uni-duesseldorf.de/abteilungen/aap/gpower3.) [27]. Based on the effects of previous RCTs, we expected a small effect group x time (repeated measures) of 0.2 for the comparison of three groups (assuming an alpha level = 0.05, two-tailed, β = 0.95, correlation between measurements = 0.5). Results of the power analysis indicated a required sample size of 36 participants per group, for a total of 108. The data will be analyzed with the intent-to-treat (ITT) approach using the last value carried forward and including all patients who intended to participate, regardless of whether they dropped out or not.

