#### Additional variables

Several additional variables are assessed in order to examine potential mechanisms of treatment and to assess feasibility and treatment fidelity.

Satisfaction with treatment as a measure of feasibility is evaluated with 10 items on an 11-point scale (0 = strongly disagree, 10 = absolutely agree). In addition, the therapists assessed feasibility in a qualitative manner including a standardized dropout evaluation and assessment of adverse effects.

All therapy sessions are documented within a table, including notes and information about the participants based on evaluations of the therapists or supervision. The therapist also notes when he or she thinks that the assigned treatment approach is not fully adequate for this patient. Furthermore, a standardized dropout evaluation was developed. If a patient breaks off treatment, an independent research assistant asks the participant standardized questions about the reasons for refusing the treatment and possible adverse effects of treatment.

Sessions will be evaluated for treatment fidelity by a research assistant blind to treatment conditions. The fidelity evaluation is based on the approach of Leeuw and colleagues who developed a method of assessing treatment delivery in clinical trials (MATD) [30].

Treatment expectancy and rationale credibility is measured with the credibility and expectancy questionnaire (CEQ) [50].

The therapeutic alliance is measured on an 11-point scale including 13 items (0 = strongly disagree, 10 = absolutely agree).

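### T2 and T3 are dated only by completing treatment, so patients who break off have no endpoint date, although the intention-to-treat analysis includes them by carry-forward

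*Protocol article*

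**What the plan says.** Under Data collection the protocol article lists a baseline assessment (T0) and three later ones. T1 comes "after 10 sessions (T1, completion of EXP short"; the last two come "upon completion of the intervention (T2), and six months following completion of treatment (T3". The Methods part of the abstract gives follow-up the same anchor: "at six months following completion of treatment".

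The Research questions ask about effectiveness, and about short versus long exposure, at post-treatment and at six months. These are T2 and T3.

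The Sample size calculation section describes an "intent-to-treat (ITT) approach using the last value carried forward", "including all patients who intended to participate, regardless of whether they dropped out or not". The Data analysis section adds that intention-to-treat analysis is "used to account for deviations from random allocation and missing data".

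For patients who stop, Additional variables describes one procedure: "If a patient breaks off treatment, an independent research assistant asks the participant standardized questions about the reasons". It goes on to possible adverse effects. No outcome questionnaire is named.

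Two other statements matter. Questionnaires are filled in at home over the internet (Data collection). A weekly online survey contains, among other items, the PDI, the QBPDS and a numeric pain rating (Process evaluation).

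**The concern.** The schedule and the analysis set do not fit together. The analysis covers every patient, but the endpoint dates exist only for those who finish. Followed as written, the plan puts an early value in place of the post-treatment and six-month outcomes of patients who break off, even where a patient would have answered the questionnaire.

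Loss of the endpoint is then tied to stopping treatment, and stopping is unlikely to be unrelated to tolerance or response. The arms may also differ in how often and why patients stop. The section on the unique features of EXP makes exposure depend on the patient accepting the rationale and being willing; no such step is described for CBT-P. That is a reason to expect a possible difference, not evidence of one. At stake is the comparison in the first two research questions.

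**Working it through.** **Step 1: apply the schedule to a patient who breaks off.** Session counts are from Table 1, triggers from Data collection.

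| Break-off | EXP_short (10 sessions) | EXP_long and CBT-P (15 sessions) |
|---|---|---|
| Before session 10 | No trigger met for the completion assessment or T3; latest scheduled value is T0 | No trigger met for T1, T2 or T3; latest scheduled value is T0 |
| After session 10, before session 15 | Cannot occur, treatment is complete | T1 reached; no trigger for T2 or T3; latest scheduled value is T1 |

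So no arm has a T2 or T3 date for a patient who breaks off. The carried value can also be of a different kind by arm: always baseline in EXP_short, baseline or T1 in the two longer arms.

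**Step 2: see whether another stated measurement fills the gap.** The weekly survey could give PDI, QBPDS and pain values up to break-off. The article does not say that it continues afterwards, or that its values may be carried forward or used as T2 or T3. It lists neither the two-week pain diary nor the four-week DSF rating, which are the pain measures under Primary outcome measures. A value from before break-off is in any case not a six-month value.

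**Step 3: number affected.** The plan gives 36 patients per group, and 3 x 36 = 108. It states no dropout rate, so there is no plan figure to reproduce. With an assumed rate *d*, the number per arm is 36 x *d*:

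- *d* = 0.10: 36 x 0.10 = 3.6, about 4 per arm (108 x 0.10 = 10.8 in total)
- *d* = 0.25: 36 x 0.25 = 9 per arm (108 x 0.25 = 27 in total)

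**Step 4: how this reaches the comparison.** In arm *a*, let *d_a* be the proportion without an observed endpoint, *c_a* their mean carried-forward change from baseline, and *v_a* the mean change they would have shown if assessed at the endpoint. The arm mean is then off by *d_a*(*c_a* - *v_a*), and the difference between exposure (E) and CBT-P (C) by

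*d_E*(*c_E* - *v_E*) - *d_C*(*c_C* - *v_C*).

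This is zero if dropouts do not change after their last value, or if the two products are equal. If the gap *g* = *c* - *v* is the same in both arms, the error is (*d_E* - *d_C*)*g*. With the ends of the assumed range in opposite arms it is (0.25 - 0.10)*g* = 0.15*g*, in either direction. The article gives no value for *g*, so the size of any bias cannot be stated.

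**Step 5: can dates be set for these patients?** Yes. The Intervention section specifies weekly appointments, so the last session is nominally due 10 - 1 = 9 weeks after the first in EXP_short and 15 - 1 = 14 weeks after it in the other two arms. T3 follows six months later.

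**The case against.** The strongest reply is that this is a condensed article giving the nominal schedule, and that nothing in it says dropouts are refused the T2 and T3 questionnaires. That is correct. A reader might infer that the endpoint is never measured in patients who stop, that every measurement after baseline depends on sessions, or that the dropout contact serves only to record reasons and harms. The documents support none of these. They are silent on questionnaires after break-off, they describe a weekly survey with both disability scales and a pain rating, and they state what the dropout interview asks without excluding anything else.

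What remains is not just silence. The article states a trigger that a patient who breaks off cannot meet, and states that gaps are filled by carry-forward. Those two rules together give a poorer endpoint than the available alternative.

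A second reply is that timing by sessions and completion serves the trial's purpose: T1 after 10 sessions holds dose constant, and the comparison of 10 with 15 sessions needs that. This stands. Moving every assessment to a calendar date would trade one problem for another, and there is no need to move T1 or the timing for completers.

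Third, some who stop treatment may leave the study altogether, as Ethical considerations allows. This also stands: the remedy will recover some endpoints, not all, and the article gives no basis for saying how many.

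**Conclusion.** The point holds in a limited form. T2 and T3 are defined by completing treatment, no assessment date is defined for patients who break off, and the analysis nevertheless includes these patients by carrying an earlier value forward. If stopping, or what happens after it, differs between arms, the comparisons at T2 and T3 may be biased.

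The figure of about 4 to 9 patients per arm rests wholly on an assumed 10-25% dropout rate, and it counts every dropout as lacking an observed endpoint, which the article does not say. Neither the direction nor the size of any bias can be derived from the document. The change should be made: the weakness touches the main comparison and the remedy uses what the trial already has.

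**What to change.** Leave T1 session-based, and leave T2 and T3 completion-based for patients who finish. Add a rule for patients who stop treatment early but have not withdrawn consent:

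1. T2 is due in the week the arm's last session was due (session 10 in EXP_short, session 15 in EXP_long and CBT-P). T3 is due six months after that.
2. Send the same online questionnaires, including the pain diary and the DSF rating, on those dates.
3. At the existing dropout contact, ask the patient to stay in follow-up, and record stopping treatment separately from withdrawing consent.
4. Use the observed T2 and T3 values in the intention-to-treat analysis in place of carried-forward ones, and state whether weekly values may be used where T2 or T3 is still missing.

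The cost is an amendment to the schedule and a modest follow-up effort, without new staff or visits. Some patients will not respond. According to Trial status, 71 of 108 patients had been randomised by May 2013. The rule can therefore apply in full to the remaining 108 - 71 = 37, and to earlier dropouts only where their T2 or T3 date has not passed. Report how many dropouts fall under each arrangement, by arm.
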